**Data Management & Analysis**

Data collection at baseline and follow-up will be conducted as above in “Methods” section.

Data management will be conducted using REDCap as detailed above. This is a confidential and secure database protected on UT servers.

Formal comparative analysis will follow the intent-to-treat principle. Primary analysis will compare the intervention and control groups by using multiple linear regression analysis. The model will include DQI score as the response variable and, as explanatory variables, a binary indicator for the intervention group and 7 binary indicator variables representing the 8 strata in order to reflect the stratified randomization design. Additionally, as a secondary analysis, we will compare treatment decisions between the intervention and control groups by using multiple logistic regression. The model will include the treatment decision as the binary response variable and the same explanatory variables as in the linear regression model. Depending on the uptake of the intervention, additional analyses will follow the “per-protocol” principle wherein the main treatment variable will be whether the Joint Insights tool was used.

For analysis of the 3- and 6-9 month data, we will fit linear mixed models for continuous outcomes35 and generalized estimating equations logistic regression models for binary outcomes36, including indicator variables for time point, for treatment group, and for the interaction between the two (yielding treatment effects at 3 months and at 6-9 months). Owing to the balanced design, it will be possible to fit an unstructured correlation model to eliminate any sensitivity to correlation model misspecification.

Data monitoring is not required for this study. No interim analysis is planned.

This is a minimal-risk study. Although we don’t anticipate any adverse events, any adverse events will be reported to the local IRB.

The datasets used and/or analyzed during the current study are available from the corresponding author on reasonable request.

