***Eligibility Criteria***

Inclusion Criteria (to be checked during huddle/ after check-in and x-ray/ at consent):

1. All new patients with a presumptive diagnosis of knee OA
2. Aged between 45 and 89
3. K-L grade of 3 or 4 (moderate to severe)
4. KOOS JR scores 0-85
5. Able to provide informed consent

Exclusion Criteria (to be checked during huddle/ after x-ray and check-in/ at consent):

1. Prior total knee replacement
2. Prior consultation with an orthopaedic surgeon for TKR
3. Prior experience with Joint Insights
4. Patients undergoing consideration for revision joint replacement
5. Patients seeking care for a trauma condition, or psoriatic/rheumatoid arthritis
6. Non-English or Non-Spanish speakers
7. Patients with BMI below 20 or above 46

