***Allocation***

Sequence Generation: REDCap algorithm (see details below)

Concealment: Sequence concealed by REDCap algorithm

Implementation: Research Assistant (see protocol below for Randomization)

Blinding: Unblinded/ no masking

For the randomization, we will stratify by variables known or suspected to be predictive of decision quality and/or treatment choice by using stratified random block randomization. Participants will be stratified by 3 factors: ethnicity (Hispanic/non-Hispanic), insurance (public safety net insurance/other insurance) and attending surgeon. Block randomization will occur within each stratum with random block sizes of 4 and 6, and an equal number of patients assigned to the intervention and control arms within each block. These steps are carried out automatically in the REDCap study database. This strategy ensures that participants are equally distributed to treatment and control through time, therefore controlling for any time varying effects that may occur. The Dell Medical School Biomedical Data Science Hub will oversee the randomization.

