      - Click on the “Select OA severity” dropdown menu to select the radiographic severity (KL 3 or 4)
      - Show the results with the patient and explain that they will receive a printed-out version for discussion with their provider
      - Leave the room
      - Print out the score report(s) and hand to the provider or hang in the basket on the exam room door
      - Inform the provider the patient is ready to be seen
      - Write the patient’s “Benefit” percentage under “notes” on the clinic whiteboard
- During the provider consultation
  - Research assistant must record for REDCap:
    - The number of minutes the counseling provider was in the room
      - This includes [name], [name], the Arthroplasty Fellow, Advanced Practice Providers (APPs).
      - As much as possible, the amount of time should only reflect time spent on the shared decision making conversation; this means that time spent on injections does not count, and time spent collecting medical history should not contribute either
      - However, we recognize there is variation in which provider or learner contributes to each part of the visit – for instance a learner (medical student or resident) might collect history for some patients which will *not* be included in the final time calculation, while the APPs might collect history for others and this *will* be included
      - Ultimately, we just record the exact number of minutes any of the above providers who are listed specifically by name spend in the room *except* after they come out to grab an injection and go back in to perform the injection
    - Enter the total consultation minutes into the appropriate field in REDCap
  - If the exact timing is missed, RA will confirm an estimate with the provider

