***Study Methods: Baseline Documentation***

The following steps must be completed by the researcher at the baseline visit to ensure proper documentation:

- On Box
  - Completion of the “Joint Insights Eligibility Tracker” as above
  - Completion of the “Joint Insights Follow-Up Tracker” for all enrolled patients
  - Completion of the “Joint Insights Dashboard” with total number of patients enrolled
- On REDCap
  - Completion of all baseline surveys (in “Event 1” column)
    - Complete “KOOS, JR” using Athena
    - Complete “PROMIS-10” using Athena
  - Mark which knee is primary in the 3-month “Follow-Up KOOS, JR” field
  - Mark which knee is primary in the 6-9 month “Follow-Up KOOS, JR” field
  - Schedule emails for the 3- and 6-9 month follow-up visits for patients preferring emails rather than phone calls
    - Schedule for a date 7 days before the 3-month follow-up date
    - Set up to 2 recurring reminders, each 7 days apart
    - Use the [[contact]](mailto:[contact]) email as the sender
    - Use the “Email Template” found on Box for the body of the email
      - Change [NAME] to the patient’s last name
      - Change [DATE] to the patient’s 3-month follow-up date

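### The treatment-decision model is fixed without baseline KOOS JR and K-L grade, so a valid secondary analysis may be less efficient than it could be

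*Protocol*

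**What the plan says.** The primary analysis in the Protocol (Data Management & Analysis) is a linear regression of the DQI score on an arm indicator and "7 binary indicator variables representing the 8 strata in order to reflect the stratified randomization design". For the treatment decision the same section names a logistic regression and fixes its covariates by reference: "The model will include the treatment decision as the binary response variable and the same explanatory variables as in the linear regression model".

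The Allocation section defines the strata: "Participants will be stratified by 3 factors: ethnicity (Hispanic/non-Hispanic), insurance (public safety net insurance/other insurance) and attending surgeon". It gives the reason for choosing them: "we will stratify by variables known or suspected to be predictive of decision quality and/or treatment choice". Knee severity is not among them.

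Both severity measures are inclusion criteria (Eligibility Criteria): "K-L grade of 3 or 4 (moderate to severe" and "KOOS JR scores 0-85". At the baseline visit the researcher must also "Complete “KOOS, JR” using Athena" in REDCap (Study Methods: Baseline Documentation).

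**The concern.** The covariate set was written for the DQI score and carried over unchanged to an outcome with different drivers. How badly the knee is affected, on the radiograph and by the patient's own report, is a likely influence on whether a patient chooses replacement. The Protocol itself treats radiographic severity as relevant to that choice. In the Full Tool steps the researcher uses a "dropdown menu to select the radiographic severity (KL 3 or 4" on the surgery benefit and risk report (Recruitment Methods: OM1 Enrollment & Delivery).

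In a logistic model, adjusting for a strong baseline predictor raises the power of the test of treatment. The rate of surgical treatment is a stated objective, and the trial was not sized for it. Efficiency that can be had from data already collected is therefore worth having.

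**Working it through.** **1. Are the covariates available before randomisation?** The Eligibility Screening section has the researcher confirm all criteria, after imaging and check-in, before approaching the patient. Consent and REDCap randomisation follow. The Full Tool script says that the patient has already answered the survey questions at check-in. The Interventions section lists baseline KOOS JR only under the intervention arm, but eligibility needs the score in everyone and Baseline Documentation has it entered for enrolled patients. Both values therefore precede allocation in both arms.

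**2. The plan's own figure.** The only sample size stated is for the DQI: effect size 0.5, alpha 0.05 (two-sided assumed), power 0.90.
- Normal approximation: n per arm = 2(1.960 + 1.282)²/0.5² = 84.1, so 85, or 170 in all.
- A t-based calculation gives 172.
- The stated 180 gives power of about 0.92, and 180/0.90 = 200 to enrol.

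The 180 is slightly generous and otherwise consistent. No power is stated for the treatment decision, so there is nothing to reproduce for it.

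**3. Simulation of the treatment-decision model.** From the Protocol: 200 patients, 1:1 blocked allocation within 8 strata, logistic regression. Assumed, because the Protocol gives no values: the surgery rates by arm, half of patients at K-L 4, KOOS JR normally distributed, unequal stratum sizes and modest stratum effects. Severity effects are odds ratios for K-L 4 vs 3 and per SD of KOOS JR. They are none (1, 1), weak (1.5, 1.25), moderate (2, 1.5), strong (3, 2) and very strong (4, 2.5). Each scenario had 2,000 trials and a two-sided Wald test at 0.05.

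Power with strata only → with both covariates added:

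| Severity effect | 50% vs 30% | 40% vs 25% | 40% vs 20% | 50% vs 35% |
|---|---|---|---|---|
| None | 0.851 → 0.850 | 0.659 → 0.658 | 0.881 → 0.883 | 0.591 → 0.591 |
| Weak | 0.840 → 0.840 | 0.611 → 0.616 | 0.892 → 0.892 | 0.615 → 0.621 |
| Moderate | 0.843 → 0.863 | 0.622 → 0.650 | 0.888 → 0.899 | 0.620 → 0.634 |
| Strong | 0.841 → 0.892 | 0.630 → 0.687 | 0.889 → 0.923 | 0.582 → 0.650 |
| Very strong | 0.839 → 0.906 | 0.643 → 0.748 | 0.878 → 0.932 | 0.583 → 0.678 |

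Gains in percentage points across the four rate pairs:
- none or weak: −0.1 to 0.6
- moderate: 1.1 to 2.8 (2.0 at 50% vs 30%, 2.8 at 40% vs 25%)
- strong: 3.4 to 6.8 (5.1 and 5.7 for the same two pairs)
- very strong: 5.4 to 10.5

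The Monte Carlo standard error of one power figure is √(0.84 × 0.16/2000) = 0.008 at power 0.84. Both models were fitted to the same simulated trials, so the differences are more precise than that.

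**4. The gain in patients, 50% vs 30%.** This is the squared ratio of mean log odds ratio over standard error.
- Moderate: (0.97/0.323)² / (0.90/0.307)² = 1.05, or about 5% more patients.
- Strong: (1.07/0.341)² / (0.90/0.306)² = 1.14, or about 14%.

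**5. Error rate.** With 40% in both arms and strong severity effects (4,000 trials), rejection was 0.053 with strata only and 0.057 with the covariates. The Monte Carlo standard error is √(0.05 × 0.95/4000) = 0.003.

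**6. At 180 patients, 50% vs 30%.** Moderate 0.789 → 0.815, strong 0.807 → 0.863. The picture is the same.

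**The case against.** The strongest reply is that nothing here is wrong. The Protocol stratifies on variables it believes predictive and adjusts for exactly those, so the analysis follows the design. This is a secondary outcome for which no power is promised, and the gain depends wholly on assumed rates and associations. Eligibility limits K-L to two grades, which narrows the prognostic range. All of this stands, and it keeps the point at efficiency. What remains is that the Protocol itself closes the covariate set, so this is a stated choice, and that the covariates cost almost nothing if severity turns out to matter little.

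Three stronger readings are tempting, and the documents do not support them.

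- *The strata-only odds ratio is biased toward 1.* In the simulations it does lie nearer to 1 (mean log odds ratio −0.90 against −1.07 in the strong 50% vs 30% case). That is non-collapsibility: the two odds ratios are different, equally valid quantities.
- *Chance imbalance in severity invalidates the comparison.* With 90 per arm and half at K-L 4, the standard error of the difference is √(2 × 0.25/90) = 7.5 points, so a gap of 10 points or more would arise in about 18% of trials. The error rate of the test already allows for such gaps.
- *K-L grade is not recorded for control patients.* The only entry described for enrolled patients is in the Full Tool steps. However, the Randomization section has staff complete three items of a form that evidently has more, and its figure is not shown. The grade must also be read in controls to confirm eligibility. A missing field is not established.

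It is also unclear whether the treatment decision is the choice at the visit or surgery by a later date, since neither the Outcomes table nor the analysis section gives a time. This decides whether 200 or 180 is the relevant number, but not the conclusion.

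**Conclusion.** The point holds as one of efficiency. The treatment-decision model leaves out two likely predictors that eligibility requires before randomisation. The planned strata-only test is valid. Under the assumed surgery rates, adding KOOS JR and K-L grade gains about nothing if severity is weakly prognostic, 1 to 3 points of power if moderately and 3 to 7 if strongly, with type I error near nominal. Very strong associations would give more, but nothing in the Protocol shows that they apply. The size is uncertain because the Protocol states neither a surgery rate nor a severity association. The change is worth making because it is cheap, uses data already collected and loses almost nothing if severity proves unimportant.

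**What to change.** In Data Management & Analysis, add to the treatment-decision logistic model, beside arm and the stratum indicators, baseline KOOS JR (continuous) and K-L grade (4 vs 3). Define both for the primary knee and as established at eligibility screening, so that patients with bilateral pain are handled by a stated rule. Report the model-standardised risk difference together with the odds ratio.

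Use the K-L grade read at screening in both arms. For patients already enrolled, take it from the existing record, because a new field completed before randomisation could not cover them. The Protocol lists recruitment as open and plans no interim analysis, so on its own account the change can still be prespecified.

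The cost is a few sentences of text, retrieval of a grade already read, two more model parameters, and a conditional odds ratio that differs from the strata-only one. The risk difference is there to give readers a marginal effect.

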This study evaluates a technology-enabled decision aid (OM1, Boston, MA, USA) that provides evidence-based education (i.e. on understanding the condition, treatment options and comparisons, patient values and question & answer quiz), preference assessment, and personalized, quantifiable benefit-risk ratio alongside the level of potential benefit in relation to joint stiffness, joint pain and quality of life. The study will be performed in the setting of an integrated care system providing patient-centered care for hip and knee OA over the full cycle of care.

The impact of a technology-enabled decision aid incorporating predictive analytics with machine learning capabilities on decision quality, activation, experience & functional outcomes of patients in this setting is relatively unknown. As a comparator or control group, this study will utilize identical evidence-based educational materials but will exclude the personalized risk ratio report and preference assessment.

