***Interventions***

Intervention Arm: “Full Tool”

- Prior to consultation with a provider patients experience:
  - Demographic survey
  - Patient reported outcomes surveys:
    - PROMIS-Global 10
    - KOOS JR
  - OM1 Joint Insights educational module
  - OM1 Joint Insights preferences module
  - OM1 Joint Insights score report
- During consultation with a provider patients experience:
  - Discussion about the results of the decision aid
- Immediately after consultation with a provider patients experience:
  - Decision quality and satisfaction surveys:
    - DQI
    - CollaboRATE
    - DCS
    - Satisfaction score
- 3 and 6-9 months after consultation with a provider patients experience:
  - Decision quality surveys
    - DRS
  - Patient-reported outcomes surveys
    - KOOS JR
    - PROMIS-Global 10
  - *Patients may request to leave the study at any point without repercussion*
  - *Patients are contacted via phone, email, text, and/or Athena MyChart*
  - *Patients may participate in any concomitant care or interventions without limitation*
- 6-9 months after consultation with the provider and completion of all follow-up surveys:
  - Patients receive via mail or email a $25 gift card

Control Arm: “Education Only”

- Prior to consultation with a provider, patients experience:
  - OM1 Joint Insights educational module
- During consultation with a provider patients experience:
  - Standard care *without* discussion of the OM1 Joint Insights modules
- Immediately after consultation with a provider patients experience:
  - Decision quality and satisfaction surveys
- 3 and 6-9 months after consultation with a provider patients experience:
  - Decision quality surveys
  - Patient-reported outcomes surveys
  - *Patients may request to leave the study at any point without repercussion*
  - *Patients are contacted via phone, email, text, and/or Athena MyChart*
  - *Patients may participate in any concomitant care or interventions without limitation*

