***Recruitment Methods: OM1 Enrollment & Delivery***

After Randomization, leave REDCap and open instead the online OM1 platform in a new browser tab. Follow the procedure below to enroll the patient and open the education:

- Click “Add Patient” in the top menu bar
- Complete only the fields in the REGISTRATION and CONTACT PREFERNCES sections marked with an Asterix *
  - First name
  - Last name
  - Date of birth
  - Sex at birth
  - Language Preference
- Click “Continue”
- Complete all fields in the CARE TEAM section
  - Organization (UT Health Austin)
  - Physicians ([name] vs [name])
  - Musculoskeletal (L vs R knee)
- Click “Save”
- Complete all fields with an Asterix * in the [RIGHT/LEFT] KNEE section
  - Type
    - “TKA Consultation” if patient is in Group A / Full tool
    - “TKA Education” if patient is in Group B / Educational materials only
  - Event date (today)
  - Facility (UT Health Austin)
  - Physician ([name] vs [name])
  - *If patient is randomized to the Full Tool, the below fields will also appear, which the researcher will then complete using the medial chart or by speaking directly with the patient:*
    - Height (manually enter from chart)
    - Weight (manually enter from chart)
    - Tobacco use (select one)
    - Comorbidities (select all that apply)
    - #ED visits in the last year
    - #Hospitalizations in the last year
- Click “Save”
- The following screen will automatically appear after a few moments:

[figure not shown]

- - Click the dropdown menu “Send PRO to” and select “transfer to paper”

[figure not shown]

- - Enter the patient’s birth date and today’s date to open the module
  - The educational module will automatically appear, and the researcher will then hand the iPad to the patient for them to navigate through at their own speed. Researchers will use the following script:

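### The additional analysis called per-protocol is an as-treated comparison by tool use, with an ambiguously worded exposure; intention-to-treat stays primary

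*Protocol*

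**What the plan says.** Under Data Management & Analysis, the protocol states: "Formal comparative analysis will follow the intent-to-treat principle". The primary linear model for the DQI score contains "a binary indicator for the intervention group and 7 binary indicator variables representing the 8 strata", so its treatment variable is randomized arm. The same paragraph then makes a further set of analyses conditional on uptake and calls them per-protocol. It describes this as a "principle wherein the main treatment variable will be whether the Joint Insights tool was used". It gives no uptake threshold and does not say which component counts as use.

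Under Interventions, the list of what patients receive before the consultation contains "OM1 Joint Insights educational module" in both arms. Only the intervention arm adds the preferences module and the score report. The control consultation is to take place without "discussion of the OM1 Joint Insights modules". The Background describes the control as using "identical evidence-based educational materials but will exclude the personalized risk ratio report and preference assessment". Under OM1 Enrollment & Delivery, control patients are registered on the same platform, with an education entry type chosen "if patient is in Group B / Educational materials only".

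**The concern.** A per-protocol analysis restricts the sample to patients who followed their assignment and still compares them by randomized arm. Here the treatment variable itself is replaced by what the patient used, which is an as-treated analysis. A patient randomized to the full tool who did not use it is counted with the controls.

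Use is not randomized. Patients work through the module at their own pace, and staff are told what to do if someone has not finished. Time, literacy and engagement could plausibly affect both completion and the DQI score. If non-users would have scored lower in any case, moving them raises the user mean and lowers the comparison mean, and a benefit can appear where none exists.

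Two features add to this. The wording does not say whether the educational module, which both arms receive, counts as use. And the analysis is run or omitted after uptake has been seen, without a stated rule. A reader is also likely to give more weight to a result labelled per-protocol than to one labelled as-treated.

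**Working it through.** **No figure of the plan to reproduce.** The protocol gives neither an uptake rate nor a prognosis gap for non-users. The only figure used from it is the design effect of 0.5 SD (Sample Size), as a yardstick.

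**1. What the exposure can mean.**
- *Any Joint Insights module.* Both arms receive the educational module, so the exposure equals 1 for essentially everyone. The model then has 8 columns for the strata (intercept plus 7 indicators) and one constant exposure column: 9 columns of rank 8. The effect cannot be estimated.
- *The full tool (preferences module, score report).* The exposure is 0 in controls and in full-tool non-users, and 1 in full-tool users. The effect can be estimated, but the contrast is not the randomized one.

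**2. Bias under the full-tool reading when the tool has no effect.** Assumptions: n per arm; a share q of patients would not use the tool if offered it, equal in both arms by randomization; these patients score δ SD lower; the rest have mean 0.
- Users: n(1 − q) patients, mean 0.
- Comparison group: n controls with mean −qδ, plus nq full-tool non-users with mean −δ. Its mean is −(nqδ + nqδ)/(n + nq) = −2qδ/(1 + q).
- As-treated bias = 2qδ/(1 + q). With δ = 0.5 this is q/(1 + q).
- Bias of a true per-protocol set (full-tool users against all controls) = 0 − (−qδ) = qδ.
- Intention-to-treat bias = −qδ − (−qδ) = 0.

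| Non-use q (assumed) | As-treated bias (SD) | Share of design effect 0.5 | Two-sided 5% test rejects | Per-protocol-set bias (SD) |
|---|---|---|---|---|
| 5% | 0.05/1.05 = 0.048 | 10% | about 6% | 0.025 |
| 15% | 0.15/1.15 = 0.130 | 26% | 14% | 0.075 |
| 20% | 0.20/1.20 = 0.167 | 33% | 19% | 0.100 |
| 30% | 0.30/1.30 = 0.231 | 46% | 32% | 0.150 |

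The rejection rates come from simulated trials with 100 per arm, no treatment effect and an unadjusted t-test. The simulated biases at 15%, 20% and 30% (0.128, 0.165, 0.230) agree with the formula.

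**3. A second model.** Here non-use depends on a continuous trait correlated 0.3 to 0.5 with the score, with 90 per arm, 5% to 30% non-use and no true effect (20,000 trials per setting). As-treated bias ran from 0.06 to 0.38 SD, with rejection rates from 6.7% to 70%. Intention-to-treat bias was about 0, with rejection at about 5%. The per-protocol set was biased by 0.03 to 0.25 SD.

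**4. The instrumental-variable alternative.** With use possible only in the full-tool arm, the complier effect is approximately the intention-to-treat difference divided by the uptake 1 − q. Under no effect it is 0/(1 − q) = 0. Its interval is wider by about 1/(1 − q): 1.05 at 5% non-use, 1.18 at 15% and 1.43 at 30%.

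**The case against.** The strongest reply is that this is a wording defect in an optional analysis. Intention-to-treat is primary, the disputed analysis is additional, and no primary or secondary comparison depends on it. That stands, and it limits the severity.

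A reader might infer that the exposure is simply true in both arms, so that the analysis has no contrast. The documents do not support this as fact. The sentence opens by referring to uptake of the intervention, the arms are named Full Tool and Education Only, and the randomization scripts give software to the first group and educational materials to the second. The full tool is the likely meaning. What remains is that the sentence does not say so, and the likely meaning leads directly to the as-treated problem.

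The size is also open to challenge. Non-use rates and the 0.5 SD deficit are assumptions. Delivery is supervised: staff open the module, return, offer more time, generate the report and show it. Non-use could therefore be low, and at 5% the bias is only about 0.05 SD. This is a fair limit on magnitude, though not on direction if non-users have the worse prognosis.

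A reader might also infer that poor uptake would lead to this result being promoted over the primary one. Nothing in the text says so.

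Finally, the alternatives have limits. A restricted per-protocol set is itself biased, as the table shows. The complier estimate needs assignment to act only through use of the tool. Open-label delivery strains that assumption. So would a definition requiring both preferences module and report, since a patient receiving one of them would count as unexposed. These points shape the fix.

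An unseen statistical analysis plan might define use. It would not undo the protocol's choice to put use in place of randomized arm under a per-protocol label.

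**Conclusion.** The point holds in limited form. The analysis is mislabelled: it is as-treated and abandons the randomized comparison. Its exposure is ambiguous, with the full tool the likely meaning. The primary intention-to-treat conclusion is unaffected.

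Under a true null and an assumed 0.5 SD deficit in non-users, the upward bias is about 0.05 SD at 5% non-use, 0.13 at 15% and 0.23 at 30%. If use is unrelated to prognosis, there is no such bias under the null. Severity: should be fixed, not must be fixed.

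**What to change.** Replace the per-protocol sentence along these lines: *Regardless of uptake, a complier average causal effect will be estimated by two-stage least squares, with randomized arm as instrument and the 7 stratum indicators as covariates. Use means receipt of any component available only in the full-tool arm (preferences module or score report).* State the exclusion restriction, note that open-label delivery strains it, and note that the interval is wider than the intention-to-treat interval.

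If a per-protocol set is also wanted, define it as patients who received their assigned arm's components, analyse it by randomized arm, call it supportive and note its potential selection bias. Label any regrouping by actual use as as-treated and exploratory.

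Two supporting changes are needed:
- Record receipt of the preferences module and of the score report for each patient. The Baseline Documentation list contains neither, and the delivery steps check completion of the educational module only.
- Reconcile the delivery step under OM1 Enrollment & Delivery that describes the patients not on the full tool as receiving education plus preferences with Interventions, which gives controls education alone. The definition of use depends on this.

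The cost is a few sentences, two data fields and one extra model. For patients already enrolled, receipt may have to be recovered from platform records, and the protocol does not say whether these hold it.
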